### START in the third sector

While our dissemination work has resulted in START's wider availability, this has not yet been optimised for varied reasons. These include lack of money, available staff and fit with existing NHS

service structures (10). In places where START has been implemented there are waiting lists for the treatment because of the huge number of carers who may potentially benefit. It is important to consider how to support more carers and to build upon existing third sector infrastructure, as many prefer interventions in a non-health setting. If availability were extended, including to the third sector, then many more carers could benefit. Although the AS currently deliver complementary services to carers and a wealth of experience and knowledge exists in the third sector, non-evidence based interventions often dominate. Developing pathways for START delivery in the third sector would help bridge this gap.

#### START for Minority Ethnic (ME) groups and the South Asian community

Although the START intervention and manual have been standardised and made available online with a training programme for trainers (see <http://www.ucl.ac.uk/psychiatry/start>), they have not been adapted or tested with different ethnicities and cultures. Minority ethnic (ME) people have specific needs related to culturally different understanding of dementia and consequent late presentation, which we have detailed in our earlier qualitative study (11). Barriers to help-seeking for dementia in ME groups vary greatly (12-15) and include negative experiences and feelings about services, stigma, and reluctance to reveal private or sensitive information, share or relinquish family care to people outside the family circle (16-18). These may mean that ME people miss out on support provided by services and feel isolated due to lack of awareness of service availability and appropriateness to their culture (19). By the time people contact services, people living with dementia may have higher care needs and families may already be coping with severe behavioural changes. Thus, ethnicity and culture have a unique relationship with the dementia care pathway, and affect how patients and carers respond to health interventions.

In this project, we will build the foundations to adapt the START intervention and manual for the South Asian population in the UK. Alzheimer's Society have successfully delivered a four session programme about dementia to South Asian carers (Information Programme for South Asian Families) through bilingual workers. Our Bradford collaborators' evaluation of this programme found that community partners with established reputations and in-depth knowledge about culturally acceptable and effective recruitment strategies played an essential role (20). START is flexible and has different components, with diverse strategies that enable it to be individually tailored to carer circumstances and changing needs. There may be the need for cognitive reframing of the intervention, emphasising the benefit to the person with dementia, rather than a relinquishing of responsibility or prioritising the carer's emotional needs (21). Consideration of pleasant, stress-relieving activities may need to consider the wider family support network, as well as support from local religious and community organisations (13). Furthermore, as the people living with dementia present later, different symptoms have to be considered and the balance of time devoted to initial orientation and discussion may need to shift in favour of more targeted coping strategies. The intervention may require more emphasis on rights and financial benefits to respond to greater socio-economic need for some, and to enable carers to be assertive with care providers if their needs are not taken seriously due to racism. Moreover, there are sometimes, but not always, language barriers that may need to be addressed with the use of bilingual facilitators.

## **3 OBJECTIVES**

### **3.1 Primary Objectives**

To lay the foundations for widening access by

- Providing a framework for implementing and delivering START in the third sector.
- Adapting START for Minority Ethnic (ME) communities, starting with the exemplar of the South Asian community.

### 3.2 Secondary Objective

Provide a template for both the third sector and other minority ethnic groups facing similar barriers to deliver the START intervention

## 4 STUDY DESIGN

This is a mixed methods study designed to assess implementation of a modified START intervention for family carers of relatives with dementia, within existing structures of the Alzheimer's Society and the South Asian community. The total study duration is 36 months from study set up through to write up (see Figure 2). The study will be carried out in three phases, with some overlap between phases.

### 4.1.1 Phase 1

Our first implementation framework will be used prior to beginning implementation to describe and guide the process (22). We will use the widely employed Consolidated Framework for Implementation Research tool (CFIR) (22, 23), a structured tool with five domains, divided into a total of 35 defined constructs, to ensure the team systematically assesses potential barriers and facilitators in preparation for implementation. The CFIR provides a pragmatic structure for approaching complex problems of implementation. We will, as recommended, start by explicitly selecting and justifying which of the CFIR constructs we will use (22, 23).

We will undertake focus groups or individual interviews as appropriate and consult with Alzheimer's Society stakeholders and family carers of relatives with dementia from South Asian backgrounds (using translators as appropriate), to inform changes to the START intervention.

#### *\*Consent procedures\**

Informed consent will be sought from all participants taking part. Participants will be informed that all data collected will be anonymised and that their personal information will be kept confidential although the data will be used for research. We will ask for the participants' permission to audio-record the focus groups and individual in-depth interviews, and inform them that the audio tapes will be destroyed at the end of the study. Participants will be informed that they can withdraw their consent at any time. In seeking consent, we will follow the Mental Capacity Act (2005) provisions when deciding whether to include people and will not include those who do not have capacity. Trained mental health researchers will conduct the interviews. We will use focus groups (for Alzheimer's Society staff and South Asian carers) or individual interviews as appropriate. If the participant becomes upset or distressed, we will offer to stop the interview and check that they are willing to proceed before continuing with the interview.

#### *\*Training and delivery\**

Our project researchers are psychology graduates. They have a degree in psychology but without clinical psychology training. They have been recruited on evidence of listening skills, empathy and dementia experience and have experience in qualitative work and have attended training and are supervised in their work. This level of expertise will ensure breadth of skills. A short training programme will be delivered by our leads. Project researchers have all completed UCL training in safety and diversity and training in Good Clinical Practice and informed consent. They will also have teaching sessions dedicated to cultural sensitivity. Training will emphasise the need to operate from an inclusive values base and to respect diversity and the existing knowledge and experience of those they interview.

We will then use a process model, the Knowledge-to-Action (KTA) Framework (24) to design a practical strategy for translating our findings into practice, incorporating what we have learned of the context and situation in which we are implementing through the CFIR (22). The KTA Framework

is a process intended to guide the process of translating research into practice and has an emphasis on stakeholder involvement and tailoring knowledge to the needs of those who are going to use it. The Framework contains two distinct but mutually influencing components, one focused on Knowledge Creation and one called the Action Cycle. The Action Cycle reflects the practical actions needed to apply knowledge in practice. The Framework includes consideration of how to adapt knowledge to local context, assessment of barriers to knowledge use, and tailoring of interventions – we will be doing this in detail through our use of CFIR in the first phase. As the cyclical nature of the Framework suggests, our work to explore and understand context using CFIR and to ensure effective implementation through the KTA Framework will involve iterative elements rather than a simple linear process.

We will scope the training needs of the potential Alzheimer’s Society and South Asian therapists as they will have different training and support needs than the psychology graduates we had for START. We will make changes to the training manual and START manuals for the third sector as needed. We will change the START manuals (carer and therapist version) words and illustrations using the knowledge generated to fit with South Asian culture and time of presentation. We will also produce training materials. We will then consult with people whom we have interviewed in the Knowledge to Action phase to refine it further. We will employ translators to translate and back-translate the manuals from English to Punjabi as the most common South Asian language. We will employ translators to “smooth out” inaccuracies iteratively until it is correct.

Changes will result in a modified START intervention for the Third Sector (TS) “**RE START TS**”, and for the South Asian (SA) Community “**RE START SA**”.

#### 4.1.2 Phase 2

In Phase 2 (month 12 to 30) we will train three (n=3) Alzheimer’s Society Dementia Advisers (DA) to deliver RE START TS to nine (n=9) family carers of relatives with dementia from the Alzheimer’s Society, and project researchers/bilingual facilitators to deliver RE START SA to three (n=3) South Asian carers in Punjabi, and to between eight and ten (n=10) South Asian carers in English.

#### 4.1.3 Phase 3

In Phase 3 (month 20 to 33) [name] will lead evaluation to assess the impact of the intervention incorporating qualitative and quantitative information covering the fields of the MRC process evaluation framework (25). He will use the RE-AIM implementation tool (or best suited equivalent) which specifies the aspects of implementation that should be evaluated specifically:

- Reach (rate of acceptance and demographics of those taking it up, participants’ views of experience, unexpected and expected),
- Effectiveness (dose – number of sessions delivered to individuals; fidelity – using session recording; baseline and post-intervention mood – The Hospital Anxiety and Depression scale(HADS) (26, 27), and Quality of Life, Health Status Questionnaire (HSQ) (26, 28) as in START(7),
- Adoption (Developing diverse partnerships)
- Implementation (training documents and manuals for further implementation)
- Maintenance (embedding in long term infrastructure)

RE-AIM (29) has previously been used in the USA in similar projects (30). Evaluation will be independent: the researcher who delivers the intervention will not be the one who evaluates. Although there will be summative aspects to this evaluation, in an important sense it will be formative, in that it will inform subsequent implementation and spread of START. We also anticipate that what we will learn things from this project about how to implement evidence-based practice in dementia care in diverse community settings in ways that go beyond the specifics of START.

To promote sustainability beyond the end of the grant, we will revisit implementation sites towards the end of the project to assess the sustainability of our implementation work. We have engaged an NHS trust medical director as co-applicant and the London dementia network as collaborators. We will publish our work in peer reviewed journals, present it at conferences and work with the AS to publicise it. The AS is committed to promoting it in the voluntary sector if successful, by holding workshops for voluntary sector providers and commissioners to learn about START and access resources.

Figure 2 GANTT chart

[figure not shown]

### Participant groups and sampling procedure

We will use a purposeful sampling technique widely used in qualitative research for the identification and selection of information rich cases for the most effective use of limited resources, and to achieve a depth of understanding (31). We will sample participants to capture maximum variation in sociodemographic characteristics, and other variables including time in post at the Alzheimer's Society, relationship to relative with dementia (e.g. spouse or child) and living situation. We will obtain a comprehensive understanding by continuing to sample until no new substantive information is acquired (theoretical saturation). We will collect socio-demographic information on all participants included in the study. The interviews will be audio tape-recorded and transcribed verbatim. We will use a topic guide derived from the literature which will develop further during the interviews in an iterative fashion (32). The data will be qualitatively analysed using thematic analysis to identify broad similarities and differences in the data.

Phase 1 participant groups will inform the adaptation of the START intervention and materials, and include (i) up to ten (n=10) Alzheimer's Society nominated Dementia Advisers, (ii) up to ten (n=10) Alzheimer's Society nominated managers and (iii) up to twenty (n=20) family carers of relatives with dementia from South Asian backgrounds. Phase 2 participant groups include (i) three (n=3) Alzheimer's Society nominated Dementia Advisers who will be trained to deliver the RE START TS intervention to (ii) up to nine (n=9) Alzheimer's Society nominated carers and (iii) up to thirteen (n=13) family carers of relatives with dementia from South Asian backgrounds who will receive the RE START SA intervention, delivered by project researchers in English or a South Asian language.

### Enrolment (duration) and follow up

Participants recruited to Phase 1 of the study will be enrolled from consent through to finalisation of the manuals at month 16, i.e. approximately 13 months including follow up (i.e. consultation on changes to the intervention). Participants recruited to Phase 2 will be enrolled from consent through to completion of the evaluation at month 33, i.e. approximately 22 months including follow up (i.e. post intervention quantitative measures and interviews). Participants can withdraw from the study at any time, and data collected up to this point will be included. This will be recorded using an exit form.

## 5 STUDY SCHEDULE

Recruitment will commence subject to necessary approvals, following procedures described in section 8 of this document. We will obtain informed consent from all participants including

Alzheimer's Society staff and family carers of relatives with dementia, following procedures described in section 6 of this document.

In **Phase 1** (See Figure 3), we will interview Alzheimer's Society stakeholders (i.e. Dementia Advisers and Managers nominated by the Alzheimer's Society) and family carers from South Asian backgrounds about the START intervention using the Consolidated Framework for Implementation Research Tool (CFIR) (22, 23) to assess baseline barriers and facilitators, and scope voluntary sector and bilingual facilitators' training and support needs. Participants will be interviewed following consent at a location convenient to them or at UCL. The Knowledge-to-Action framework (KTA) (24) will be used as a guide for translating these findings into practice, i.e., designing the RE START TS, RE START SA interventions and materials. Work to explore and understand context using the CFIR and to ensure effective implementation through the KTA framework will involve iterative elements rather than a simple linear process. We will follow up with Phase 1 interviewees to consult on changes and further refine interventions and materials.

In **Phase 2**, we will (i) train and supervise AS Dementia Advisers to deliver RE START TS to AS nominated family carers and (ii) train and supervise researchers and bilingual facilitators to deliver RE START SA to family carers from South Asian backgrounds in English or in a South Asian Language. It is difficult to provide extensive detail regarding training, supervision and delivery procedures as these will be determined in large part by Phase 1 results. However, procedures are likely to be some variation of those followed in previous studies in which START has been delivered (7).

In **Phase 3**, [name] (University of Exeter) will lead the evaluation will use the RE-AIM (Reach, Effectiveness, Adoption, Implementation, and Maintenance) implementation framework (29) (or best suited equivalent) to assess the impact of the intervention incorporating qualitative and

quantitative information. To monitor fidelity to the manualised intervention, facilitators will record one session per family carer. Quantitative measures (see below) will be administered to carers prior to the intervention, immediately after the intervention and at one year. Follow up with Phase 2 participants will also include interviews about the intervention immediately after using the RE-AIM evaluation framework as a guide.

We will use validated standardised quantitative measures to inform the evaluation (and see if the changes are those expected from the original study) administered to carers prior to the intervention, i.e., at Baseline (B), immediately after the intervention (T1) and at one year (T2). Quantitative measures will include:

- (i) The Hospital Anxiety and Depression Scale (HADS) (26, 27), a validated, reliable measure to measure mood in carers.
- (ii) The carer Health Status Questionnaire (HSQ) (28), a 12 item health-related quality of life scale.
- (iii) The widely used Client Receipt Services Inventory (CSRI) (33), to measure the service use consequences for the carer and the relative with dementia.

**Figure 3 Study phases, theoretical frameworks and procedures**

| Study Phases                                                | Implementation Framework                                                                           | RE-START TS
(Third Sector)                                                                                                                                                                                                                                                                  | RE-START SA
(South Asian ME Group)                                                                                                                                                                                                                                                                                                               |
|-------------------------------------------------------------|----------------------------------------------------------------------------------------------------|------------------------------------------------------------------------------------------------------------------------------------------------------------------------------------------------------------------------------------------------------------------------------------------------|-----------------------------------------------------------------------------------------------------------------------------------------------------------------------------------------------------------------------------------------------------------------------------------------------------------------------------------------------------|
| Phase 1
Exploratory/Scoping
& Design
(Months 1-18) | Consolidated Framework for
Implementation Research tool (CFIR) /
Knowledge-to-Action (KTA)   | Phase 1 qualitative interviews with Alzheimer's Society
Dementia advisers and Managers

Scoping AS Dementia Adviser training needs

Design RE START TS Package (manuals, training
materials)

Consult with Phase 1 interviewees on changes | Phase 1 qualitative interviews (South Asian Family
Carers)

Scoping Bilingual Facilitator needs

Design RE START SA Package (manuals, training
materials)

Translate and Record RE START SA Package

Consult with Phase 1 interviewees on changes                                  |
| Phase 2
Delivery of Training
(Months 12-30)           | (Reach, Effectiveness, Adoption,
Implementation, and Maintenance)
RE-AIM Implementation Tool | Administer pre-training quantitative measures
(CSRI, HADS, HSQ) - Baseline

Train three (3) AS Dementia Adviser to deliver RE START
TS

Supervise delivery of RE START TS to nine (9) AS
carers                                                      | Administer pre-training quantitative measures
(CSRI, HADS, HSQ) - Baseline

Train Bilingual Facilitators to deliver RE START SA

Deliver RE START SA in South Asian Language to
three (3) South Asian carers

Deliver RE START SA in English to bwn eight and ten (8-
10) South Asian carers |
| Phase 3
Evaluation
(Months 20-33)                     |                                                                                                    | Administer post-training quantitative measures
(CSRI, HADS, HSQ) - T1 and T2

Post-training qualitative interviews (AS Dementia
Advisers and Family Carers)                                                                                                          | Administer post-training quantitative measures
(CSRI, HADS, HSQ) - T1 and T2

Post-training qualitative interviews (Bilingual Facilitators
and South Asian Family Carers)                                                                                                                                                 |

## 6 CONSENT

Members of the research team will obtain individual informed consent from all participants including Alzheimer's Society staff and family carers of relatives with dementia, at a location convenient to them. Prospective participants who have agreed to participate in the study will be asked to sign a consent form prior to data collection. Potential participants will be given no less than

24 hours from receipt of the participant information sheet, before being contacted by a member of the research team to consent or not to take part. In seeking consent, we will follow the Mental Capacity Act (2005) provisions when deciding whether to include people and will not include those who do not have capacity. Participants will be informed that all data collected will be anonymised and that their personal information will be kept confidential according to the Data Protection Act and according to UCL information governance procedures, although the data will be used for research. We will ask for participants' permission to audio-record focus groups and semi-structured interviews, and at least one (1) training session. We will make clear that audio data files will be destroyed at the end of the study. Participants will be informed that they can withdraw consent at any time without being obliged to provide a reason. If one is offered, it will be recorded by the research team. Non-native English speaking family carers of relatives with dementia will be approached by a bilingual member of the research team and/or a member of the research team accompanied by a translator.

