## 8 RECRUITMENT

Dementia Advisers in both phases will be identified and nominated by the Alzheimer's Society, as will managers and carers. Family carers of relatives with dementia from South Asian backgrounds will be identified and approached via the London Dementia Network, Camden and Islington NHS Foundation Trust Memory Services, and Bradford based community organisations with whom co-applicant [name] has collaborated with in previous studies.

The Alzheimer's Society will provide nominated staff and carers with Participant Information Sheets, and refer prospective participants to the research team. The research team will make contact no less than 24H later, provide further details regarding the study if needed and extend an invitation to participate in the study.

In the case of family carers of relatives with dementia from South Asian backgrounds, some prospective participants may have already agreed to be contacted for research (as trusts may have a register), but we will still approach a clinician beforehand to ensure there have been no changes and ask, if possible, if they can initiate contact. Clinicians or social workers will provide prospective participants with Participant Information Sheets (PIS) detailing the purpose of the study and what participation in the study entails, and obtain verbal consent and/or confirmation for referral to the research team. Participant Identification Centres will be asked to verbally provide potential

participants details. In cases where written information is provided in hard copy or electronically, these will be stored following procedures outlined above, and any emails permanently deleted immediately after. The research team will make contact no less than 24H later, provide further details regarding the study if needed and extend an invitation to participate in the study. Members of the research team will obtain informed consent from all participants that have agreed, following procedures described in section 6 of this document.

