## 12 DATA HANDLING AND MANAGEMENT

This project has been registered with the UCL Data Protection Team (registration number: Z6364106/2018/01/57). All information gathered will be kept strictly confidential and held in accordance with the principles of the Data Protection Act (1998), and according to UCL information governance procedures. Alzheimer's Society staff will work in accordance with the Alzheimer's Society data handling and management procedures.

Hard copy data of participant consent forms will be stored at the Division of Psychiatry, UCL, in a secure locked location accessible only by researchers.

Each participant will be assigned a unique identifying number the key of which will be kept electronically in the study's UCL shared drive accessible only by the UCL research team. All data will be stored without subject name or contact details. Data will be held on a secure database on a password-protected computer at University College London. Access to data will be restricted to appropriate members of the research team. In order to enable follow-up contacts, it will be necessary to identify the participants, but access to contact details (e.g. name and address) will be restricted to key members of the research team.

Participants will be informed how data will be managed as part of the consent procedure. Rules governing the conduct of the focus groups will be discussed at the beginning of each group and participants will be requested not to discuss others' contributions outside the group.

Audio recordings from focus groups/interviews and training sessions will be uploaded to the UCL Data Safe Haven as soon as possible after they are acquired. Once uploaded recordings will be

deleted from recording devices. Audio files will be sent to a professional UK-based commercial transcription service (WAY with Words) that has strong data protection, confidential storage and removal from the transcription service database when complete. After data processing the data will be archived and stored securely in accordance with UCL protocols.

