### **15 ASSESMENT AND MANAGEMENT OF RISK**

In delivering the intervention to family carers of relatives with dementia, Dementia Advisers will work according to the Alzheimer's Society's Risk Management policies. An important aspect of supervision of the researchers delivering the intervention to family carers from South Asian backgrounds will be to identify and respond to any risks identified during the course of assessment or intervention. Researchers will be provided with specific training in how to respond to any risks disclosed by carers, in relation to harm to both themselves and the person they were caring for. Researchers will be asked to speak to the lead investigator if the abuse Modified Conflict Tactic Score (MCTS) (34, 35) is in the possibly abusive range ( $\geq 2$ ) or if they had any concerns about potential abuse. Similarly, if carers reported high levels of depression or anxiety, this will be discussed with the lead investigator. If concerns are raised, a plan will be made with the lead investigator about how to manage the risk and information will be shared with the local clinical teams. Time will also be taken within supervision to highlight the importance of behaving ethically and safely in all aspects of clinical work, for example reflecting on maintaining clear boundaries

clinically and how to practise safely when working alone in people's homes. Researchers will work to UCL's Lone Working standard in cases where they visit the family carer at their home.

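### The consent statement says all data are anonymised and personal information is confidential, but section 12 keeps a linking key and section 15 shares risk information with clinical teams

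*Protocol*

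**What the plan says.** **What participants are told.** Section 6 (Consent), which covers all participants, says: "Participants will be informed that all data collected will be anonymised and that their personal information will be kept confidential". It then qualifies the confidentiality part only, as "kept confidential according to the Data Protection Act and according to UCL information governance procedures". The consent text in section 4.1.1 (Phase 1) makes the same anonymisation statement and adds that "their personal information will be kept confidential although the data will be used for research", without mentioning the Act or UCL procedures. Section 12 (Data handling and management) describes all gathered information as held in strict confidence.

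**How the data are held.** Section 12 also says: "Each participant will be assigned a unique identifying number the key of which will be kept electronically in the study's UCL shared drive". It continues: "In order to enable follow-up contacts, it will be necessary to identify the participants". Research data are stored without names or contact details, and access to identifiers is restricted to the research team.

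**When information leaves the team.** Section 15 (Assessment and management of risk) asks researchers to go to the lead investigator about possible abuse or high levels of depression or anxiety. If concerns are raised, a management plan is made and "information will be shared with the local clinical teams".

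**The concern.** Sections 4.1.1 and 6 do more than describe a general policy on privacy: they set the content of what participants will be told. If staff follow them as written, a carer hears that the data are anonymised and that personal information is confidential, and hears of no circumstance in which it could be passed on. The same plan keeps the means to identify that carer and, in defined circumstances, passes information about them to a clinical team.

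Two things are at stake. The first is whether consent rests on an accurate account of how data are held. The second is the position of the researcher when a concern arises: following section 15 departs from what the carer was told, and holding to what the carer was told departs from section 15. The protocol should not put staff in that position.

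**Working it through.** No stated figure has to be reproduced and no error rate or power is involved. The check sets the passages side by side, then counts who is affected.

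**1. Anonymised or coded?**
- Statement (sections 4.1.1 and 6): all data collected are anonymised.
- Practice (section 12): a number for each participant, an electronic key, and identification when follow-up requires it. The protocol gives no date for destroying the key.
- The link is needed by design. Section 5 measures the same carers at baseline, immediately after the intervention and at one year. Section 4 keeps Phase 2 participants enrolled for about 22 months, and Phase 1 interviewees are consulted again on changes.
- Data that the team can relink to a person by a key it holds are pseudonymised. The statement and the practice disagree for as long as the key exists.

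**2. Confidential with or without exception?**
- Statement (sections 4.1.1, 6 and 12): confidential, in section 12 strictly so. None of the three names an exception for risk.
- Practice (section 15): information goes to local clinical teams if concerns are raised. To be of use there, it must identify the carer.
- Section 4.1.1 sits under Phase 1, whereas section 15 concerns carers receiving the intervention in Phase 2. The sharpest clash on this limb is therefore between section 15 and sections 6 and 12.

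**3. How many people?**
- Anonymisation statement: every group listed in section 4. Sum: 10 + 10 + 20 + 3 + 9 + 13 = 65, which matches the target of up to 65 in the study summary.
- Clinical-team route: section 15 introduces it for researchers delivering the intervention to South Asian carers, at most 13 (section 4).
- Background rate: section 2 gives up to 40% of family carers with clinical levels of depression and anxiety.
- Upper figure on mood grounds: 0.40 × 13 = 5.2, or about 5 carers.
- The nine Society carers are treated by Dementia Advisers, who work to the Society's own risk policies. Those policies are not reproduced in the protocol, so no count is made for this group.

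**The case against.** The best case for the plan has four parts.

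- **Section 6 is qualified.** It ties confidentiality to the Data Protection Act and UCL procedures. That is true, and it would be wrong to call section 6 wholly unqualified. But naming a legal framework does not tell a carer that a concern about abuse or mood may be passed on, and section 4.1.1 lacks even that.
- **The information sheet may cover it.** Section 12 says data management will be explained during consent, and the sheet is not among the documents. It may already describe the key and the risk exception, so one cannot say that participants are in fact left uninformed. If it does, however, it conflicts with protocol text that dictates a different statement, and the protocol still needs correcting.
- **Data handling is careful.** Storage without names, restricted access and the bar on moving identifiable data between sites are sound practice. They reduce the risk; they do not make coded data anonymous.
- **Sharing is conditional.** A discussion with the lead investigator stays inside the team, and information goes out only if concerns are raised. This limits the number affected, not the inconsistency.

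A reader might also infer more than the text supports:

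- *That nomination of the three advisers breaks the promise.* The Society does nominate them, employs them and funds the study. But nomination contradicts neither statement, and nothing says that the Society receives transcripts or attributable data. Recognition within a group of three (the Phase 2 advisers, or the carers treated in Punjabi) is at most a separate risk to note.
- *That fear of recognition biases the delivery findings upward.* This is conjecture; the protocol offers no evidence for it.
- *That holding voice recordings contradicts the promise.* Participants are told that recordings are made and are destroyed at the end of the study.
- *That about 9 carers could be affected.* This applies 40% to all 22 Phase 2 carers (0.40 × 22 = 8.8) and overlooks the separate route in section 15 for the nine Society carers.

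**Conclusion.** The point holds as an internal contradiction between what participants are to be told and what the plan does. On anonymisation, the statement does not match section 12. On confidentiality, the accurate description is that sections 4.1.1, 6 and 12 state no exception although section 15 contains one; to call the confidentiality promise simply untrue would go further than the documents allow.

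The first part reaches every participant, up to 65. The second reaches at most about 5 carers at the background rate. That figure assumes that all 13 South Asian places are filled, that the up-to-40% figure applies to these carers, that clinical levels correspond to the high levels in section 15 (which it does not define), and that every such carer's case leads to sharing. It covers the mood triggers only: the protocol gives no rate for abuse concerns. The hard ceiling for the route as introduced is 13.

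Section 9 plans descriptive summaries only, and none of them depends on this. The case for acting is the accuracy of consent and a clear footing for staff who have to disclose.

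**What to change.** Reconcile the passages by changing the consent and confidentiality wording, leaving the section 15 procedure as it stands:

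1. In sections 4.1.1 and 6, replace the anonymisation statement with one saying that data are coded, with a key held by the UCL research team so that participants can be contacted for follow-up.
2. In the same two sections, state that confidentiality is subject to the risk-disclosure procedure in section 15, and that participants are told this before they consent.
3. In section 12, qualify the strict confidentiality statement with a cross-reference to section 15.
4. Check that the information sheet says the same, and correct it if it does not.

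The cost is protocol wording and, if needed, information-sheet wording. Sample, measures, analysis and risk procedures are unchanged. One possible downside is that some carers will speak less freely about mood or conflict once they know of the exception; that is the price of an accurate statement.
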